## Abstract

**Background:**

Hepatic encephalopathy (HE) is one of the most important severe complications of liver cirrhosis. Thought to be caused by elevated blood levels of gut-derived neurotoxins (particularly ammonia) entering the brain, HE manifests as a wide range of neurological or psychiatric abnormalities, which increase the risk of mortality, result in substantial morbidity and negatively affect the quality of life (QoL) of both patients and their caregivers. HE is also associated with a substantial economic burden. Rifaximin-α 550 mg is a locally acting oral antibiotic that reduces the effects of ammonia-producing intestinal flora, and which is used to help reduce the recurrence of overt HE. The efficacy of rifaximin-α 550 mg was established in a randomised controlled trial and long-term extension study. However, ‘real-world’ evidence is also required to assess how this efficacy may translate into effectiveness in clinical practice, including the potential impact of treatment on healthcare resource utilisation.

**Methods:**

The Prospective Real-world Outcomes Study of HE Patients’ Experience on Rifaximin-α 550 mg (PROSPER) is a multinational, multicentre, observational study that will be conducted under real-world clinical practice conditions. Comprising a retrospective phase (up to 12 months) and a prospective phase (up to 24 months), and employing a robust statistical methodology, PROSPER has been specifically designed to minimise the bias associated with observational studies. The primary endpoint will be the effect of rifaximin-α 550 mg treatment on HE- and liver-related hospitalisation rate and duration of hospitalisation. Secondary endpoints will include comprehensive assessments of the impact of treatment on the QoL and workplace productivity of patients and caregivers, a global assessment of treatment effectiveness and safety/tolerability. Approximately 550 patients will be enrolled.

**Conclusions:**

PROSPER will provide valuable real-world information on the effectiveness of rifaximin-α 550 mg in reducing the recurrence of HE, and its impact on the QoL and work productivity of patients and their caregivers. By providing data on both the direct costs (e.g., hospitalisation rate, duration of hospitalisation) and indirect costs (such as work productivity) of HE, PROSPER should help confirm whether rifaximin-α 550 mg treatment represents a good use of economic resources.

**Trial registration:**

ClinicalTrials.gov identifier NCT02488993.

## Introduction

Hepatic encephalopathy (HE) is a brain dysfunction caused by liver insufficiency and/or portosystemic shunting, which manifests as a wide spectrum of neurological or psychiatric abnormalities [1]. It is now widely recognised as one of the most important severe complications of liver cirrhosis, along with conditions such as ascites and variceal bleeding [1]. HE severity is categorised using West Haven criteria from ‘minimal’ through grade 1 to 4 [1]. ‘Covert HE’ is defined as West Haven minimal and grade 1, and ‘overt HE’ is defined as West Haven grades 2 to 4 [1]. Overt HE occurs in 30–40% of patients with cirrhosis at some time during their clinical course [1]. HE increases the risk of mortality [2] and is one of the most debilitating complications of liver disease [1], negatively affecting the lives of both patients and caregivers [1, 3].

HE is also associated with a substantial economic burden, in terms of direct healthcare costs resulting from, for example, emergency room visits and hospitalisation [1, 4–11]. Although difficult to accurately determine, the indirect costs of HE (e.g., loss of work productivity, car accidents) also represent a substantial economic burden, which is likely to be further increased when the impact on caregivers is taken into account [3, 7, 12].

The neuropsychiatric symptoms of HE are thought to result from elevated blood levels of gut-derived neurotoxins (particularly ammonia), which enter the brain due to the inability of the cirrhotic liver to remove them from the blood [13]. Rifaximin-α 550 mg is a locally acting oral antibiotic that is minimally absorbed in the gut to reduce the effects of intestinal flora, including ammonia-producing species [14]. Its clinical activity may be due to its effects on the metabolic function of gut microbiota, rather than a change in relative bacterial abundance [15]. Rifaximin-α 550 mg is indicated in Europe for the reduction in recurrence of episodes of overt HE in patients aged ≥18 years [16]. In Australia, it has the same indication, but is restricted to where other treatments have failed or are contraindicated [17]. The efficacy of rifaximin-α 550 mg has been confirmed in a randomised controlled trial (RCT), in which rifaximin-α 550 mg twice daily (administered concomitantly with lactulose therapy in approximately 91% of patients) reduced the relative risks of recurrence of overt HE and HE-related hospitalisation by 58% and 50%, respectively, compared with placebo (absolute risk reductions: 24% and 9%, respectively) [18]. In a subsequent 2-year extension study, long-term treatment with rifaximin-α 550 mg (with concomitant lactulose in approximately 90% of patients) provided a continued reduction in the rate of HE-related and all-cause hospitalisation, without an increased rate of adverse events [19].

Although RCTs are essential in the clinical development of new treatments, they do not necessarily reflect clinical practice conditions. Typically, they are conducted in carefully defined patient populations using specific inclusion and exclusion criteria. By contrast, in clinical practice, patients are more diverse in terms of clinical characteristics than those recruited for RCTs. In addition, whereas RCTs employ rigid treatment protocols, in clinical practice treatment is tailored on a patient-by-patient basis. Consequently, ‘real-world’ studies are required to complement evidence from RCTs by determining how the efficacy of an agent translates into effectiveness in clinical practice. Since real-world studies have a higher likelihood of inherent bias than RCTs, it is important when designing a real-world study to eliminate as much bias as possible and minimise the impact of any remaining bias in the statistical analysis methodology employed. Real-world data are particularly useful for hard-to-reach patient populations (such as HE patients), for which clinical trial recruitment is challenging. Moreover, national reimbursement authorities are increasingly requesting real-world data to support evidence from clinical trials when examining the economic rationale for supporting new treatments [20, 21]. Real-world studies are therefore important both clinically and from a patient access perspective.

An important aspect of real-world studies is to assess patient- and caregiver-reported outcomes, since the effectiveness of a treatment is not only dependent on its efficacy and safety/tolerability, but also on its effects on the patient’s quality of life (QoL) and ability to function, and the associated impact on those who care for them. This is particularly true for chronic conditions, such as HE, where an agent’s effectiveness relies primarily on the patient being willing and able to be compliant with the treatment over the long term.

We here describe the design of the Prospective Real-world Outcomes Study of HE Patients’ Experience on Rifaximin-α 550 mg (PROSPER), which will evaluate the clinical effectiveness of rifaximin-α 550 mg and its impact on healthcare resources when used for the management of HE in routine clinical practice.

## Methods/design

PROSPER is a multinational, multicentre, observational study that will be conducted in secondary/tertiary care centres across Europe and Australia (ClinicalTrials.gov identifier: NCT02488993). Study site selection will be based on an initial feasibility assessment to evaluate the volume of patients seen and local expertise in HE at potential centres. The principal country for patient recruitment will be Denmark, where no ethical approval is required for observational studies. Ethical approval in other individual countries will be sought, where appropriate.

### Study design

PROSPER will be conducted under ‘real-world’ clinical practice conditions. Consequently, no changes to the management of HE patients will be made for the purposes of the study.

Once eligible patients have been recruited and consented to participate in the study, two data collection phases will be undertaken (Fig. 1). The first will be a retrospective phase, involving the review of the patients’ medical records and electronic hospital admissions data. Up to 12 months of data prior to study entry will be reviewed and collected. The level and nature of missing data will be assessed and accounted for in the statistical analysis plan, if necessary. The retrospective phase will be followed by a prospective phase, during which data will be collected from all patients either receiving rifaximin-α 550 mg (rifaximin-α 550 mg cohort) or not receiving rifaximin-α 550 mg (control cohort) from the point of study entry. Up to 24 months of data following study entry will be collected and analysed.

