### Study population

Patients with cirrhosis and HE will be enrolled into PROSPER. The study will employ a limited number of inclusion and exclusion criteria in order to reflect the diversity of patients encountered in clinical practice (Table 1).

**Table 1 Tab1:** Inclusion and exclusion criteria

Inclusion criteria	Exclusion criteria
• Diagnosis of cirrhosis	• West Haven score of ≥2 at study entry
• Age ≥ 18 years	• A mental health disorder that makes HE diagnosis questionable (e.g., dementia, psychosis)
• Enrolment within 12 weeks of resolution of an episode of overt HE associated with a hospital visit	• Prior treatment with rifaximin^a^ within 12 months prior to the qualifying overt HE episode
• Ability to provide informed consent	• Contraindications to the use of rifaximin-α 550 mg, as per the local Summary of Product Characteristics [16, 17]
• Clinical eligibility to receive rifaximin-α 550 mg, in the opinion of the participating physician, regardless of HE treatment actually received	

*HE* hepatic encephalopathy

^a^All types and dose strengths of rifaximin

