### Sample size calculation

In observational studies where multivariable modelling is expected to be performed, the study should have at least 10 events for every variable included in the model. Therefore, in order to consider approximately 10 variables, 100 events would need to be observed in each of the study cohorts (patients receiving and not receiving rifaximin-α 550 mg). On the basis of an open-label maintenance study of rifaximin-α 550 mg in patients with HE [19], approximately 45% of patients would be expected to have experienced a hospitalisation within the first 12 months of follow-up. Assuming a dropout rate of 10%, approximately 247 patients would be required for each of the two cohorts, or 494 patients overall. Thus, a total study population of 550 would be sufficient to assess the primary endpoint of the study at an interim follow-up of 12 months, with additional precision following the full 24-month follow-up period.

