### Statistical analysis

A primary aim of PROSPER will be to minimise any bias typically associated with observational studies. This will be achieved by the three-step comparative structure incorporated into the study’s design (as described above) and the associated statistical methodology. An overview of the statistical considerations is presented here.

The primary outcome of HE- and liver-associated hospitalisation rate will be analysed as a count, using either Poisson or negative binomial regression, depending on the level of observed dispersion. An offset term will be included to account for length of time eligible to experience a hospitalisation, accounting for mortality or other competing risk events. The primary outcome of duration of HE- and liver-associated hospitalisation (number of bed-days) will be analysed either as a continuous variable or a count, depending on the observed distribution. Methodologies such as median regression may be employed to account for the likelihood of right skew resulting from a small proportion of extended hospital stays. Comparison of the primary outcomes between treatment cohorts will adjust for key covariates using either multivariable regression analysis or a propensity score analysis (to be confirmed based on an exploratory review of the data). Due to the observational nature of the study, it is expected that some patients could change, discontinue or be non-compliant with therapy during the course of follow-up. These scenarios will be considered during statistical analysis and techniques that account for exposure to therapy will be applied, if applicable.

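### Cohorts are split on rifaximin-α 550 mg alone, so a patient on another rifaximin product at entry counts as a control, which can dilute comparisons 1b and 3

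*Protocol article*

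**What the plan says.** Cohort membership depends on one product. Under Study design, prospective data come from patients on rifaximin-α 550 mg "or not receiving rifaximin-α 550 mg (control cohort) from the point of study entry". The Sample size calculation repeats the split: "patients receiving and not receiving rifaximin-α 550 mg".

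The prior-treatment exclusion in Table 1 (Study population) uses a different scope. Footnote a defines rifaximin there as "All types and dose strengths of rifaximin", but the exclusion applies only to use "within 12 months prior to the qualifying overt HE episode".

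Three other statements bear on what may happen after that look-back ends:

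- Entry timing (Table 1): "Enrolment within 12 weeks of resolution of an episode of overt HE associated with a hospital visit".
- Clinical eligibility for rifaximin-α 550 mg is required "regardless of HE treatment actually received" (Table 1).
- In the study, "no changes to the management of HE patients will be made for the purposes of the study" (Study design).

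For patients who switch, stop or do not comply during follow-up, the Statistical analysis section says that "techniques that account for exposure to therapy will be applied, if applicable".

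**The concern.** The two definitions of exposure do not match. Before the qualifying episode, any rifaximin product rules a patient out. After it, only the 550 mg product counts as exposure. A patient on another type or strength at entry is taking rifaximin but falls in the control cohort.

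Three of the planned comparisons could be affected. Comparison 1b sets outcomes in the two cohorts side by side, so a control group partly on an effective rifaximin product narrows the contrast in hospitalisation rate and bed-days. Comparison 2b sets controls after baseline against the same controls before it; a rifaximin effect arising in the later period would appear as change in the control cohort. Comparison 3 takes the difference between the cohorts' pre/post changes, so it would subtract that effect from the result for rifaximin-α 550 mg.

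The Statistical analysis section makes minimising bias a primary aim, and this source can be removed by definition.

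**Working it through.** **1. Does the text admit such a patient?** Take a patient who starts another rifaximin product for the qualifying episode and is still on it at entry.

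| Rule | Result |
|---|---|
| Prior rifaximin, any type or strength (Table 1) | Not triggered: use began after the look-back window closed |
| Entry up to 12 weeks after resolution (Table 1) | Met; the exclusion does not cover this interval |
| Eligible for rifaximin-α 550 mg, whatever is actually given (Table 1) | Can be met |
| Cohort rule (Study design) | Control, because the product is not rifaximin-α 550 mg |
| Exposure techniques (Statistical analysis) | Concern change, discontinuation and non-compliance, not classification at entry |

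Nothing in the article excludes this patient from the control cohort or separates them within it.

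**2. The plan's own figure.** Inputs from the Sample size calculation: 100 events per cohort, 45% hospitalised by 12 months, 10% dropout.

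100 / 0.45 = 222.2; 222.2 / 0.90 = 246.9, rounded up to 247; 2 × 247 = 494.

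The stated 247 and 494 are reproduced. They do not depend on how other rifaximin products are classified.

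**3. Size of the dilution (illustration).** Let R be the true ratio for rifaximin-α 550 mg against no rifaximin, p the share of controls on another rifaximin product, and R_o that product's ratio against no rifaximin. If users and non-users otherwise have the same underlying rate:

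observed ratio = R / [(1 − p) + p × R_o]

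R = 0.50 is borrowed from the 50% relative risk reduction in HE-related hospitalisation quoted in the Introduction. The values of p and R_o are assumptions, since the article gives neither.

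| p | R_o = 0.50 (equal efficacy) | R_o = √0.50 (half on the log scale) | R_o = 1 (no effect) |
|---|---|---|---|
| 5% | 0.513 | 0.507 | 0.500 |
| 10% | 0.526 | 0.515 | 0.500 |
| 20% | 0.556 | 0.531 | 0.500 |
| 30% | 0.588 | 0.548 | 0.500 |

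Example: 0.50 / (0.90 + 0.10 × 0.50) = 0.50 / 0.95 = 0.526. With equal efficacy the log ratio shrinks by 3.7%, 7.4%, 15.2% and 23.4% down the rows.

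**4. Comparisons 2b and 3.** Let c be the pre/post ratio that controls would show without any rifaximin. With equal efficacy they show c × (1 − 0.5p), which is 0.95c at 10% and 0.90c at 20%. On the ratio scale, comparison 3 gives (c × 0.50) / [c × (1 − 0.5p)], the same attenuation as for 1b.

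**5. Power (illustration).** A 50% relative and 9% absolute reduction (Introduction) imply 9 / 0.50 = 18% against 9%. With all 247 per cohort analysed, no covariate adjustment and an assumed two-sided alpha of 0.05, power is 83.5% at p = 0, 80.2% at 5%, 76.3% at 10% and 67.5% at 20%, with equal efficacy. The article states no power target, so this shows direction and scale only.

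**The case against.** The strongest defence is that the two definitions serve different purposes. Footnote a belongs to a look-back exclusion, whereas the cohort rule names the exposure under study, which is one product in routine care. On that view, patients not on rifaximin-α 550 mg form a usual-care comparator, and any other rifaximin product they take is part of usual care. This would be a coherent design, but the article never states that contrast. Its Discussion says that the study should help confirm cost-effectiveness models whose comparator was placebo plus lactulose. A control group partly on rifaximin does not match that comparator.

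Several limits do stand. Medication dose and schedule are collected (Table 2), and a control's later start of another product plausibly falls under the planned exposure techniques, so the clear gap is classification at entry. Adverse events are to be judged for their relation to the medical treatment of HE, so an event related to rifaximin in a control need not be misattributed. The fuller protocol or SAP may contain a finer assignment rule; what can be said is that the rule stated here has the wrong scope.

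A reader might go further and infer that patients on rifaximin are being passed off as untreated and that every between-cohort comparison is pulled toward no effect. The documents do not support this. They never call the controls untreated, and other HE therapy is to be expected among them. They do not show that any control will take another rifaximin product, or that such a product works. Comparison 1a is a retrospective characterisation, not an outcome contrast. Confounding by indication could move the net bias in either direction.

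**Conclusion.** The point holds as a mismatch of scope in a stated rule. As written, another rifaximin product at entry makes a patient a control. This can dilute comparisons 1b and 3 and blur 2b, in proportion to how many controls use such a product and how well it works.

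The size is conditional. With a true ratio of 0.50 and equal efficacy, the observed ratio is 0.526 at 10% use and 0.556 at 20%; an apparent 50% reduction becomes about 47% or 44%. There is no dilution if no control uses another product, if that product has no effect, or if rifaximin-α 550 mg itself has none. The 0.50 is a relative risk for HE-related hospitalisation from the cited randomised trial, applied here to the broader HE- and liver-related rate, so the figures are not forecasts. At 5% to 10% use the loss is modest, about 4% to 7% of the log ratio. The definition should be corrected because the change is cheap, but the documents do not show that the study's conclusions would be overturned.

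**What to change.** For the analysis, align the cohort definition in Study design and in the Sample size calculation with footnote a of Table 1:

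- Define the control cohort as patients not receiving rifaximin of any type or dose strength at study entry.
- Report patients on another rifaximin product at entry as a separate descriptive group, outside comparisons 1b, 2b and 3.
- Add a sensitivity analysis that keeps these patients as controls. It answers the product-against-usual-care question and shows how much the classification matters.
- Count a control's later start of any rifaximin product as a change of exposure under the methods already foreseen in Statistical analysis.

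The cost is a short change of wording, using medication data already collected, and a somewhat smaller control cohort. If the 550 patients split equally, each cohort has 275, which is 28 above the required 247. Reclassifying 10% of controls (27.5) just fits. Reclassifying 20% (55) leaves 220, or 220 × 0.90 × 0.45 = 89 expected patients with an event by 12 months at the plan's own rates, against the target of 100. The number reclassified should therefore be monitored. This concerns cohort classification only and changes nothing in patient care.

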**Fig. 1 Fig1:**
[figure not shown]
Study design

In order to minimise bias and the influence of confounding factors, the study outcomes will be compared between the treatment cohorts in three ways (Fig. 1). The first approach will initially involve the clinical characterisation of the study population, based on retrospective chart review (Fig. 1, comparison 1a), following which outcomes between the cohorts will be compared after adjustment of statistical methods on the basis of the findings from comparison 1a (Fig. 1, comparison 1b). Secondly, for each cohort individually, outcomes pre and post baseline will be compared (Fig. 1, comparisons 2a and 2b). Thirdly, the difference between the two cohorts in pre/post changes will be compared (Fig. 1, comparison 3).

Patients will be eligible to enrol during or following hospitalisation for the qualifying episode of overt HE (Fig. 2; timepoint 1). Patients will also be eligible to enter the study at the time of resolution of the qualifying episode of overt HE (Fig. 2; timepoint 2) or at a follow-up appointment, providing this is within 12 weeks of resolution of the qualifying episode of overt HE (Fig. 2; timepoint 3).

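### The retrospective window contains the qualifying hospital episode and nothing excludes it, so comparisons 2a and 2b lean towards a fall without any treatment effect, and comparison 3 need not remove this

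*Protocol article*

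**What the plan says.** Four statements in the Protocol article fix the design on this point.

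- **Entry (Study population, Table 1).** An inclusion criterion is "Enrolment within 12 weeks of resolution of an episode of overt HE associated with a hospital visit". The same table excludes patients with overt HE (West Haven 2 or above) at entry, so the qualifying episode begins before entry.
- **Pre window (Study design).** "Up to 12 months of data prior to study entry will be reviewed and collected". The window is anchored to study entry, not to the episode. The prospective window runs for up to 24 months after entry.
- **Comparisons (Study design, text at Fig. 1).** Within each cohort, pre is set against post: "Secondly, for each cohort individually, outcomes pre and post baseline will be compared (Fig. 1, comparisons 2a and 2b". Then: "Thirdly, the difference between the two cohorts in pre/post changes will be compared (Fig. 1, comparison 3".
- **Purpose (Statistical analysis).** On minimising bias: "This will be achieved by the three-step comparative structure", together with the associated statistical methods.

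The primary outcomes are the HE- and liver-related hospitalisation rate, to be modelled by Poisson or negative binomial regression with an offset for time at risk, and the resulting bed-days. Enrolment is also permitted while the patient is still in hospital for the qualifying episode. The article does not say whether that episode counts as an outcome, or how a stay that spans entry is divided.

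**The concern.** Patients are selected on having just had an event of the kind that the primary endpoint counts. Followed as written, the pre window holds one such episode for each patient by the entry rule, while events after entry occur only at the background rate. A fall from pre to post is then built into both cohorts whatever the treatment does. In 2a it would look like benefit from rifaximin-α.

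Comparison 3 is the natural remedy, because both cohorts carry the artefact. Whether it works depends on the scale of the comparison and on how alike the cohorts are. They are formed by clinical choice, so equal background rates cannot be assumed.

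At stake are two of the three comparison steps on the primary endpoint, in a study that the Discussion expects to inform payors.

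**Working it through.** **The plan's own figure.** The Sample size calculation states that "100 events would need to be observed in each of the study cohorts", that "approximately 45% of patients would be expected to have experienced a hospitalisation within the first 12 months of follow-up", and "Assuming a dropout rate of 10%, approximately 247 patients would be required for each of the two cohorts". Check: 100/0.45 = 222.2; 222.2/(1 − 0.10) = 246.9, rounded up to 247; 2 × 247 = 494. The figures reproduce and are not in question.

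**Inputs for the bias**
- Background rate L. From the plan's 45%, assuming a constant rate: L = −ln(1 − 0.45) = 0.598 per patient-year. The range 0.45 to 1.7 is assumed. Its upper end is the mean number of admissions in the 12 months after initiation in the UK retrospective study described in the Discussion.
- Share f of qualifying visits that count as an admission in the pre window. The article does not give it, and a hospital visit need not be an admission. Assumed 1, with a range of 0.5 to 1.

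**Comparisons 2a and 2b with no treatment effect**, 12 months on each side: pre = L + f, post = L, apparent rate ratio = L/(L + f).

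| L per year | f | Rate ratio | Apparent fall |
|---|---|---|---|
| 0.598 | 1 | 0.598/1.598 = 0.37 | 63% |
| 0.598 | 0.5 | 0.598/1.098 = 0.54 | 46% |
| 0.45 | 1 | 0.45/1.45 = 0.31 | 69% |
| 1.7 | 1 | 1.7/2.7 = 0.63 | 37% |
| 1.7 | 0.5 | 1.7/2.2 = 0.77 | 23% |

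**Comparison 3 with no treatment effect** (R = rifaximin-α cohort, C = control).
Additive scale: difference in changes = f_C − f_R.
Ratio scale: [L_R/(L_R + f_R)] / [L_C/(L_C + f_C)].

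- Equal rates, f = 1 in both: additive 0, ratio 1.00. It cancels on both scales.
- Assumed rates 0.9 (R) and 0.6 (C), f = 1 in both: additive 0; ratio (0.9/1.9)/(0.6/1.6) = 1.26. With the rates reversed, 0.79. It cancels on the additive scale only, and the ratio bias can go either way.
- Equal rates of 0.598, f = 1 (R) and 0.75 (C): additive 0.75 − 1 = −0.25; ratio (0.598/1.598)/(0.598/1.348) = 0.84. It cancels on neither scale.

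**Simulation under no effect** (222 patients per cohort, gamma-Poisson counts with dispersion 1, 12-month windows, 3000 runs, two-sided 0.05)
- 2a with f = 1: rejects in about 100% of runs. With the episode left out: 5.0%.
- Comparison 3, rates 0.9 and 0.6, f = 1: 5.3% on the additive scale and 43% on the ratio scale (41% with the rates reversed). With the episode left out: 5.3% and 5.2%.
- Comparison 3, equal rates, f = 1 and 0.75: 63% additive, 22% ratio.

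**Bed-days.** The mechanism is the same, but the article gives no length for the qualifying stay, so no size is calculated. For a patient enrolled during the stay, its bed-days fall on both sides of baseline.

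**The case against.** The strongest reply is that the article never says the qualifying episode is counted. It says what data are collected and that pre is compared with post. Its statistical section calls itself an overview, Figs. 1 and 2 are not shown, and handling of an index admission is a derivation rule that a full protocol or SAP may contain. This stands as far as it goes: counting the episode is inferred from the windows, and a reader who took it as stated would go too far. But the article does fix the window, its anchor, the entry event and the comparisons, and presents their structure as the protection against bias. Applied literally, they include the episode.

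Other parts of the reply also stand.

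- A reader might infer that comparison 3 necessarily inherits the bias. It does not: it cancels additively when both cohorts carry the same qualifying contribution, and on the ratio scale when background rates are equal as well. The article does not fix the scale of comparison 3. Only the count model, which by convention has a log link, points to ratios. Bed-days may be analysed differently.
- The 63% is near the top of the range. It takes every visit as an admission, and uses a proportion from an open-label study of treated patients as the no-effect background in both cohorts.
- A reader might see confirmation in the UK study's fall from 2.7 to 1.7 admissions, exactly one. That study compared periods around treatment initiation, not around entry after a qualifying episode, so the match shows nothing here.
- The article nowhere offers 2a alone as proof of effect, and 2b would show a built-in fall too. Comparison 1b, between cohorts after entry and with covariate or propensity adjustment, does not use the pre count as an outcome and is not affected.

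**Conclusion.** The point holds in a limited form. As written, the pre window contains a required hospital episode that the post window lacks, and nothing shown removes it. Comparisons 2a and 2b are therefore biased towards a fall in admissions and bed-days and cannot be read as treatment effects. For admissions the spurious fall is about 63% at 0.598 per year if every qualifying visit is an admission, 46% if half are, and 23% to 69% over the assumed ranges. These sizes rest on a constant background rate before and after entry, 12 months on each side, and the assumed shares.

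Comparison 3 is a conditional remedy. On the ratio scale of the planned count model it fails when background rates differ (1.26 for assumed rates of 0.9 and 0.6), and on either scale it can fail when the cohorts' qualifying contributions differ. The documents do not support the wider conclusions that comparison 3 is always biased or that the whole primary analysis is compromised.

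**What to change.** - Exclude the qualifying episode and all its bed-days from both the pre and the post counts, in both cohorts, including stays that span entry.
- Remove the corresponding person-time and let the planned offset handle the shorter pre window. Equal 12-month windows should not be required: data reach back at most 12 months from entry and entry may be up to 12 weeks after resolution, so equal windows would need earlier chart data.
- State the scale of comparison 3 and account for correlation between a patient's pre and post counts, for example with a patient-level random effect or GEE.
- Label 2a and 2b descriptive. Excluding the episode removes the built-in event, but not all regression to the mean if patients enrol after a temporary worsening.

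The cost is wording and derivation rules. Hospital admissions data are already collected and the sample size of 247 per cohort does not change. The downside is that the pre/post reductions will look smaller and the pre window is somewhat shorter.
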